**5.5 Intervention**

All infants in the NICU eligible for the study will be assigned for bathing three times a week with washcloths impregnated with 2% chlorhexidine gluconate (Clinell ® Chlorhexidine wash cloths, GAMA healthcare) during the initial 6-months study period (intervention), followed by standard bathing during the second 6-months period, then again intervention period for 6 months and standard bathing for 6-months. Total study period- 2 years.

**Inclusion criteria**: infants weighing ≥1500 grams and ≥10 days of age; parents’ informed consent

**Exclusion criteria:** infants weighing <1500 grams or <10 days of age**;** parents’ refusal to sign informed consent.

For standard bathing procedure see appendix 1.

Before the study initiation, as well as at the beginning of each study period, nurses will be instructed on the proper technique for bathing patients. Bathing will be performed according to product brochure, three times a week.

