**1. Study Synopsis**

| Protocol Title | Evaluation of the Effectiveness of Chlorhexidine Bathing in Reducing Nosocomial Infections in the Neonatal Intensive Care Unit |
| --- | --- |
| Protocol Number |  |
| Sponsor |  |
| Primary objective | To determine if daily bathing with chlorhexidine impregnated  washcloths will reduce the incidence of bloodstream infections within the neonatal intensive care unit (NICU) . |
| Study design | This is a prospective, controlled; crossover study of daily bathing with no-rinse, 2% CHG impregnated washcloths versus bathing with water/soap or water according to gestational age and weight (e.g. standard bathing). The trial will take place in the NICU.  **In the preliminary phase of the study we will establish the safety of chlorhexidine bathing using Clinell ® Chlorhexidine wash cloths on three groups of patients: term infants admitted to the NICU; late preterm infants (34-37 weeks); preterm infants 30-34 weeks of gestation. Interim analysis for adverse events will be performed after each group of patients.**  **In the subsequent phases of the study,** all infants admitted to the NICU and enrolled in the study will be bathed three times a week with Clinell ® Chlorhexidine wash cloths during the initial 6-months study period (intervention), followed by standard bathing during the second 6-months period, then again intervention period for 6 months and standard bathing for 6-months. Total study period- 2 years.  Data collection will include all bloodstream infections as well as surveillance cultures |
| Number of subjects | Approximately 800 patients in both arms  **Up to 60 patients (at least 200 patient days) in the preliminary study** |
| Study population | Infants **>=10** days ,weighing **>=1500** grams admitted to the NICU |
| Duration of participation | Duration of NICU stay OR for the duration of invasive hardware (e.g intravacular catheters, nasogastric tubes etc. ) |
| Treatment | Bathing three times a week with either:  a.2% chlorhexidine gluconate cloth  b. water/mild soap +water |
| Assessment of efficacy | The primary efficacy endpoint will be the reduction in bloodstream infections incidence during those study periods where the 2% Chlorhexidine Gluconate Cloth will be utilized.  Additional study endpoints include overall incidence of colonization with multi-drug resistant organisms (MDRO) and time to colonization |

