**5.3 Study Setting**

The study will take place in the NICU of Shaare-Zedek Medical Center

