**5.6 Outcome measures**

A. Number of BSI/CLABSI/clinical sepsis events per 1000 patient days during the intervention periods compared with the control periods.

B. Number of new patients colonized with MRSA, VRE, CRAB or ESBL per total number of patients, monthly range and variance.

C. Number of new patients colonized with MRSA, VRE, CRAB or ESBL per 1000 eligible patient days [ Total patient days – total patient days for patients identified with MDRO]

D. Time to colonization with MDRO during the intervention periods compared with the control periods.

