**5.9 Statistical analyses**

Changes in the rates of BSI and clinical sepsis will be compared between the intervention and the control period. Continuous variables will be examined with the use of two-sample t-tests and linear regression modeling, and categorical variables will be examined by means of Fisher’s exact test. Cox proportional-hazards regression model will be used to compare the time from admission until the first primary bloodstream infection , clinical sepsis or acquisition of MDRO between the control and intervention periods.

**Sample size calculation:** based on our ongoing surveillance, there are 2-3 BSI events per 1000 patients –days in our NICU. In order to detect a 50% reduction in BSI rates , we will need 37,096 patient days (18,548 in each group) in order to have 80% power to reject the null hypothesis, with 0.05 level of significance. Currently, our average annual census is 45,000 patient days. therefore, a 2-year study will have >80% power to reject the null hypothesis (the BSI rates in the control period equal the rates in the intervention period).

**For the preliminary study, we used the data in Milstone et al. ^18^ who reported no serious adverse skin reactions and an incidence of 1.2 minor skin reactions per 1000 patient days. A sample of 500 patient days will enable us to detect a ten-fold higher rate of minor skin reactions. Therefore at least 200 patient days in each group of the preliminary study (>600 patient days), would suffice.**

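### The fixed 6-month chlorhexidine–standard–chlorhexidine–standard sequence puts each arm in only one half of the calendar year, so a half-year seasonal difference cannot be told apart from the bathing effect

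*Protocol*

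**What the plan says.** Section 5.5 begins with 6 months of chlorhexidine bathing, "followed by standard bathing during the second 6-months period, then again intervention period for 6 months and standard bathing for 6-months". It closes with "Total study period- 2 years", so four 6-month periods fill the 24 months with no gap that would shift the calendar. The synopsis gives the same order: "then again intervention period for 6 months and standard bathing for 6-months. Total study period- 2 years".

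One unit takes part (Section 5.3: "The study will take place in the NICU of" one named hospital). Within a period every eligible infant has the same bathing: "All infants in the NICU eligible for the study will be assigned for bathing three times a week with washcloths impregnated with 2% chlorhexidine gluconate" in the chlorhexidine periods, and standard bathing otherwise. Calendar period alone therefore decides treatment. There is no concurrent control, no second unit in the opposite order and no randomised order.

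The first outcome measure in Section 5.6 is "Number of BSI/CLABSI/clinical sepsis events per 1000 patient days during the intervention periods compared with the control periods". Section 5.9 states that "Changes in the rates of BSI and clinical sepsis will be compared between the intervention and the control period". The only rule about period boundaries, in Section 5.7, credits events in the first two days after a switch to the previous period. It does not bear on season.

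**The concern.** A second crossover cycle ought to protect against calendar effects. Here it repeats the first cycle exactly one year later, so agreement between the two cycles says nothing about season. Any recurring half-year difference in infection rate would appear as a chlorhexidine effect, or would hide one. The sequence fixes this in advance. A statistical analysis plan written later could not fully repair it, because the trial would hold no chlorhexidine data from one half of the year and no control data from the other.

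**Working it through.** **The plan's own figure.** Section 5.9 asks for 18,548 patient days per group. For two Poisson rates, n = (z_α + z_β)²(r₁ + r₂)/(r₁ − r₂)². With r₁ = 0.002, r₂ = 0.001, one-sided 0.05 and 80% power this is (1.645 + 0.842)² × 0.003/0.001² = 18,548. At r₁ = 0.0025 and two-sided 0.05 the same formula gives 18,837, which is within 3%. The protocol does not state sidedness. The figure is used below as an input and is not challenged here.

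**Separability.** I is chlorhexidine and C is standard bathing.

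| Months | Calendar half | Planned order | I-C-C-I |
|---|---|---|---|
| 0–6 | A | I | I |
| 6–12 | B | C | C |
| 12–18 | A | I | C |
| 18–24 | B | C | I |

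- Planned order: the correlation of treatment with half-year is 1.0. The matrix of intercept, treatment and half-year has rank 2 of 3, so the two effects cannot be estimated separately.
- I-C-C-I: the correlation is 0. With half-year and linear time both included, the matrix has rank 4 of 4.
- If season is instead modelled as one annual sine/cosine pair on monthly data, R² of treatment on the pair is 0.829 under the planned order. Variance inflation is 1/(1 − 0.829) ≈ 5.9. Under I-C-C-I it is 1.0.

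**Size, under stated assumptions.** The mean control rate is 2.5 per 1000, the midpoint of the 2–3 in Section 5.9. With 18,548 days per arm, 0.0025 × 18,548 = 46.4 events are expected per arm if bathing does nothing. The test is an exact two-sided conditional Poisson test. The seasonal amplitude A is assumed, since the protocol gives none.

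- *Square wave switching exactly at the crossovers (worst case), A = 20%.* Expected events are 46.4 × 0.8 = 37.1 against 46.4 × 1.2 = 55.6, an apparent rate ratio of 0.67.
- *Sinusoid exactly in phase, A = 20%.* The mean over a half-year is A × 2/π = 0.127, so the apparent ratio is 0.873/1.127 = 0.77.
- *Sinusoid with unknown start month.* The shift is 0.127 × cos φ, averaged over all φ.

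| | No season | Sinusoid, averaged over start month | Sinusoid, in phase | Square wave |
|---|---|---|---|---|
| False positives, A = 10% | 4% | 6% | 8% | 14% |
| False positives, A = 20% | 4% | 12% | 20% | 45% |
| Power for a true halving, A = 20% | 77% | 72% | 38% (adverse direction) | 18% (adverse direction) |

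More patient days do not help. Section 5.9 cites a census of 45,000 a year, so at most 45,000 per arm over two years. At that size the worst-case false-positive rate rises to 30% (A = 10%) and 84% (A = 20%), because a biased estimate is only made more precise.

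**Trend.** Chlorhexidine periods centre on month 9 and control periods on month 15 (correlation with linear time −0.43). An assumed 10% fall per period, with g = 0.9, gives a ratio of (1 + g²)/(g + g³) = 1.81/1.629 = 1.11 under the planned order. Under I-C-C-I it is (1 + g³)/(g + g²) = 1.729/1.71 = 1.01.

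**The case against.** Four objections deserve weight, and each narrows the point.

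1. *A reader might infer that no analysis could ever adjust for season.* That goes too far. Aliasing is exact for a two-level half-year difference. A smooth annual curve is estimable, though at nearly six times the variance and only if its assumed shape is right.
2. *A reader might take 45% false positives and 18% power as the expected performance.* They require a season that steps up and down on the crossover dates, and the 18% also requires the adverse direction. With an unknown start month and a 20% sinusoid, the averages are 12% and 72%.
3. *A reader might infer that infections in this unit are seasonal, or that the design favours chlorhexidine.* The protocol shows neither. It gives an overall rate only, and no start date for the main phase.
4. *A reader might count trend as an equal fault.* It is not. Linear time correlates only −0.43 with treatment and can be modelled under the planned order. A falling rate would work against chlorhexidine, and Section 4 says rates remain high despite the national programme, so no decline is documented.

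The alternative order is not free either. I-C-C-I joins the two control periods, and treatment then correlates 0.84 with quadratic time (0 under the planned order). A mid-study outbreak, of the kind described in Section 3, would fall on one arm.

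None of this removes the structural fault: nothing in the protocol separates calendar half-year from treatment.

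**Conclusion.** The point holds as a design fault of known structure and unknown size. The aliasing of half-year and treatment follows from Sections 1, 5.3 and 5.5 for any start date and needs no assumption beyond periods that run back to back. The size rests on assumed values. With a 20% amplitude, false positives lie between 12% (averaged over start months) and 45% (worst case), against 4%. With a 10% amplitude they lie between 6% and 14%. If season in this unit is negligible, or if its peak falls at a crossover, the bias is small, but the protocol does nothing to secure either condition. Trend is a secondary matter.

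**What to change.** Before enrolment to the main phase, change the order in Section 5.5 and the synopsis so that the second year reverses the first: chlorhexidine–standard–standard–chlorhexidine or its mirror, with the starting arm drawn by lot. Add calendar half-year to the rate model in Section 5.9. Balance on linear trend comes as a by-product.

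The change costs one sentence in each of two places. Study length, number of periods, 12 months per arm and product use stay the same, and there are two switches instead of three.

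The protocol should state the downside. One arm runs unbroken for 12 months in mid-study, which exposes the comparison to an outbreak or a non-linear trend in that year. With four periods, a model with intercept, treatment and half-year leaves one period-level degree of freedom, and adding linear time leaves none. Shorter periods whose order is reversed in the second year would shorten the block and add periods, at the price of more switches.

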| Safety | Safety will be assessed through the monitoring of adverse events  associated with bathing products to include any skin rashes or  hypersensitivity reactions. |

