Recently, the Israeli Ministry of health published guidelines that endorsed the use of 2%CHG solutions for the insertion of umbilical catheters. Shortly after, a national program for the reduction of NIs in Israeli NICUs was launched and encouraged the use of bundled practices including the use of 2%CHG for insertion and maintenance of central and peripheral catheters. The rate of CLABSI and BSI remains high in the NICU despite compliance with consensus guidelines and infection control measures. Lack of evidence from randomized trials prompt us to examine the usefulness of bathing with CHG to reduce the risk of CLABSI and BSI among infants in the NICU.

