**4. Expected significance**

National data from the USA indicate that almost a quarter of very low birth weight infants will have one or more episodes of sepsis. Compared with infants without sepsis, infants with sepsis had a significantly longer hospital stay (79 vs.60 days), had a 2-fold increase in the number of days on mechanical ventilation, and had a significantly higher mortality rate (18% vs 7%)3. Another American study estimated that, on average, the cost of NICU care was $16,800 greater per infant who experienced NICU-associated BSI^[[32]](#endnote-32)^. Approximately 7% of infants, or >12,000 infants, are born prematurely in Israel every year^[[33]](#endnote-33)^. Extrapolating the American data to the Israeli NICU translates into a major health problem. The Ministry of Health and the Israel Neonatal Society have recently launched a national program aimed at minimizing the rate of NI in the Israeli NICUs^33^. In our NICU we have adopted this program and have increased staff education, active monitoring of compliance with guidelines, as well as adoption of the “search and isolate” policy, with twice a week screening of patients for colonization with MDRO.

Despite these measures, BSI rates remain high in our NICU, which prompt us to search for additional interventions such as CHG baths. The goal of the currently proposed study is to determine if universal use of a chlorhexidine based bathing system for patients in the NICU will decrease skin bacterial burden and lead to decreased horizontal transmission of MDRO.

Additionally, we hypothesize that reduced skin colonization with opportunistic bacterial

pathogens will result in a reduction in the rate of CLABSI, BSI and clinical sepsis in comparison to regular bathing procedures.

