**5.4 Preliminary study**

**In order to establish safety , we will enroll infants admitted to the NICU to three successive treatment groups , as follows: the first group will include term infants admitted to the NICU (gestational age ≥37+6 and >7 days old), the second group will include near-term infants (gestational age > 34+0 to 36+6 weeks and >7 days old) and the third group will include premature infants (gestational age >30+0 to 33+6 and >=10 days old). We intend to enroll up to 20 patients in each group, for a minimum of 200 patient days per group (see sample size estimation). All infants will be assigned for bathing three times a week with washcloths impregnated with 2% chlorhexidine gluconate (Clinell ® Chlorhexidine wash cloths, GAMA healthcare) for the duration of their NICU stay. The infant’s skin will be monitored continuously as described below (see ‘6.0 Safety and monitoring’ and appendix 2). In case of grade 3 or 4 reactions, the study interventions will be temporarily suspended, and the adverse event will be reported to the Helsinky committee and to the study steering committee. If no grade 3 or 4 reactions will be encountered after at least 200 patient days per group, enrollment to the subsequent group will be performed (e.g if no grade 3-4 reaction will be encountered for 200 patient days in group 1, we will start enrolling patients for group 2 etc.). If no grade 3-4 dermatitis is encountered in the preliminary study, we will initiate enrollment as described below (‘5.5 intervention’)**

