**6.1 Human subject research considerations**

*6.1.1 Human subjects involvement and characteristics*

This is a crossover study. The control will be the current bathing procedures in our NICU. The “intervention” will be the use of 2% chlorhexidine gluconate cloth which is FDA

approved for adult patient perioperative skin preparation and for use to reduce bacteria that can

potentially cause skin infection. ^[[39]](#endnote-39)^. The FDA states on the drug facts box of 2% CHG cloth:” use with care in premature infants or infants under 2 months of age. These products may cause irritation or chemical burns”.

Monitoring of any unexpected adverse effects or serious adverse events related to study

procedures will be the responsibility of the principal investigator and will be reported

immediately to the steering committee as well as the IRB. (see appendix c for SAE report form)

For the purposes of this research protocol *unexpected adverse events* and *serious adverse*

*events* will be defined as follows:

*Unexpected adverse event:* Any adverse reaction or experience that is not listed in the

current labeling for the drug product or investigators brochure. Known adverse reactions

to chlorhexidene containing topical products include irritation, sensitization, and generalized

allergic reactions. Chlorhexidine should be kept out of the ears and eyes.

*Serious adverse drug event.* Any adverse reaction or experience occurring at any dose that

results in any of the following outcomes: Death, a life-threatening adverse reaction,

inpatient hospitalization or prolongation of existing hospitalization and a persistent or significant

disability/incapacity.

*6.1.2 Potential risks*

Potential recognized risks of bathing with chlorhexidine include local skin irritation, allergic reaction and irritation of mucous membranes

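### The entry criteria in Protocol 5.4 and 5.5 do not exclude an infant with a known chlorhexidine allergy or a previous severe reaction, although 6.1.1 and 6.1.2 list allergic reaction as a risk

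*Protocol*

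**What the plan says.** **Who may enter.** In Protocol 5.5 the inclusion criteria are weight of at least 1500 g, age of at least 10 days and parental consent. The exclusion criteria mirror them: "infants weighing <1500 grams or <10 days of age", and parental refusal of consent. The study population row of the Synopsis gives the same age and weight limits and nothing more. Section 5.4 defines the three preliminary groups by gestational age and by postnatal age (over 7 days in the first two groups, at least 10 days in the third), with no list of exclusions.

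**What they receive.** In the preliminary phase there is no untreated group: "All infants will be assigned for bathing three times a week with washcloths impregnated with 2% chlorhexidine gluconate". In the main phase every eligible infant receives the same cloths during the two six-month intervention periods.

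**What the protocol says about risk.** Section 6.1.1 states that known adverse reactions to "chlorhexidene containing topical products include irritation, sensitization" and, further, generalized allergic reactions. Section 6.1.2 applies this to the study procedure: "Potential recognized risks of bathing with chlorhexidine include local skin irritation, allergic reaction and irritation of mucous membranes".

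**How that risk is handled.** The Synopsis says that "Safety will be assessed through the monitoring of adverse events", and its examples include hypersensitivity reactions. Section 6.0 adds daily skin checks by nurses and twice-weekly checks by study staff. Section 5.4 suspends the intervention temporarily after a grade 3 or 4 reaction.

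**The concern.** The protocol recognizes allergic reaction as a hazard of the product and plans to watch for it, but does not use that knowledge when deciding who may be exposed. The infant for whom the hazard is most foreseeable, one already known to react, meets every entry criterion once the parents consent.

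What is at stake is the safety of that infant. There is also a practical consequence in the preliminary phase. A grade 3 or 4 reaction there suspends the intervention, and moving to the next group depends on seeing none. A severe reaction in an infant already known to be at risk could therefore hold up the safety phase for a reason that screening would have avoided.

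**Working it through.** No arithmetic applies. The check is whether any visible text keeps such an infant out, and whether such an infant could exist at the time of entry.

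**Step 1. Is there an exclusion anywhere?**

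| Place in the Protocol | Criteria used | Allergy or previous reaction mentioned as a bar? |
| --- | --- | --- |
| Synopsis, study population | age, weight | no |
| 5.4 Preliminary study | gestational age, postnatal age | no |
| 5.5 Inclusion | weight, age, consent | no |
| 5.5 Exclusion | weight, age, refusal of consent | no |

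**Step 2. Does other text fill the gap?**

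- Section 5.5 says that bathing follows the product brochure. That sentence comes directly after one on teaching nurses the technique and concerns how the bath is given. It is not an eligibility rule.
- The skin checks in 6.0, the adverse event monitoring in the Synopsis and the suspension rule in 5.4 all act after the infant has been exposed.
- Consent is an entry condition in 5.5, but the criteria do not make it an allergy screen.

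**Step 3. Could a reaction be known before entry?** Three statements bear on this.

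- Entry comes after day 7 (5.4, first two groups) or from day 10 (5.4 third group, and 5.5), so there is time for earlier exposure.
- Section 3 (Background) reports that the ministry "published guidelines that endorsed the use of 2%CHG solutions for the insertion of umbilical catheters" and that a national programme "encouraged the use of bundled practices including the use of 2%CHG for insertion and maintenance of central and peripheral catheters".
- Section 4 says of the national infection-reduction programme: "In our NICU we have adopted this program".

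Section 4 does not itself mention chlorhexidine, so the link runs through the description in section 3. Taken together, these statements make exposure before entry plausible. They do not show that any infant was exposed, and still less that any infant reacted.

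**Step 4. Set risk beside eligibility.** Sections 6.1.1 and 6.1.2 name the risk, and 5.4 and 5.5 leave it out of the entry decision. The two do not contradict each other. But the eligibility rule, applied literally, leads to repeated 2% chlorhexidine bathing of an infant with the very history that the risk section warns about.

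**The case against.** The strongest reply is that the protocol contains no error here. Recognizing a risk does not conflict with eligibility by age, weight and consent, and a missing allergy line could be raised against many protocols for topical products. The affected group is also hypothetical. No allergic reaction in a neonate is reported anywhere in the document. Section 3 describes very large neonatal trials with no serious adverse events reported, and a study of 2% chlorhexidine bathing in a NICU with no adverse events. Section 6.0 cites a study in infants of at least 1500 g and at least 7 days old, close to this population, with no significant dermatitis. In practice a clinician would be likely to withhold the cloths from an infant known to be allergic, and the brochure or consent form, neither of which is visible, may say so.

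Most of this stands as a limit on size. It does not remove the point. Eligibility is a matter for the protocol and would not be left to a SAP. If clinicians withhold the cloths on their own judgment, an eligible and consented infant departs from the assigned bathing without any rule in the criteria, whereas a written exclusion settles the matter beforehand.

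Three stronger readings are tempting and are not supported:

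- A reader might infer that allergic infants would in fact be bathed. The documents show only that the entry criteria do not prevent it.
- A reader might size the hazard by counting baths. In 5.4, 200 patient days / 20 infants = 10 days on average, and 10 x 3/7 = about 4 baths. That is a group average. An infant who reacted severely would not be expected to follow it, and it says nothing about the chance or severity of harm.
- A reader might take the dermatitis counts in 6.0 (4 of 36 infants below 1000 g, 0 of 49 at or above 1000 g) as showing that an infant who reacted at a lower weight will tolerate the product later. These are counts by weight group and do not follow individual infants. They support no special rule for earlier mild irritation.

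**Conclusion.** The point holds as a minor safety improvement. As written, the entry criteria admit an infant with a known chlorhexidine allergy or a previous severe reaction to chlorhexidine, and no visible text prevents that infant from being assigned to the cloths. The number affected cannot be estimated from the documents and is probably very small. There is no effect on the primary analysis.

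The conclusion rests on two assumptions. The first is that the criteria in 5.4 and 5.5 are complete as printed, since the product brochure and the consent pages could not be examined. The second is that some infants may have met chlorhexidine before entry through the catheter practices that the national programme encourages. That is plausible but not shown.

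**What to change.** Add one exclusion line to both 5.4 and 5.5: *known chlorhexidine allergy, or a previous grade 3-4 skin reaction (Appendix 2 grading) to chlorhexidine*. Tying the second part to the grades that 5.4 and 6.0 already use for severe reactions gives it a defined threshold. The content of Appendix 2 is not visible here, so the sponsor should confirm that its scale can be applied to a reaction that occurred before entry.

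Apply the exclusion identically in intervention and control periods. If it were applied only when chlorhexidine is in use, the two sets of infants would be selected by different rules.

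The cost is one line in each section and the loss of very few infants, in both kinds of period. No change to the planned patient days is needed.

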**5.7 Data collection**

Each patient admitted to the NICU during the study periods and meeting the inclusion criteria, will be recorded and assigned a specific study number. The dates of admission and dates of discharge will be recorded and used to calculate length of stay and to determine the

incidence of nosocomial infections based on microbiological data. Clinical and laboratory data, including the use of invasive device (intravascular devices, mechanical ventilation, feeding tubes) will be collected on standardized forms. The data will be coded under a password protected database and linked only to study patient identifier.

Infections and MDRO acquisitions will be monitored during the study period. Events occurring within 2 days after the transition will be assigned to the previous bathing period.

For infection surveillance, daily review of cultures and new orders for antibiotic therapy will be performed for all study participants. Infectious events will be evaluated by an independent investigator blinded to the intervention period.

Active surveillance testing for MDRO will be performed once every two weeks during the study period. Swabs from the nasopharynx (for MRSA)] and from the rectal area (for ESBL producing organisms, VRE and CRAB) will be obtained by unit staff and processed in the microbiology laboratory of Shaare-Zedek Medical Center.

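### Parents can know the unit's current bath when they consent and only participants are followed, so consent-driven case mix may bias the primary rate comparison between periods

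*Protocol*

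**What the plan says.** **Allocation.** Protocol section 5.5 gives chlorhexidine "during the initial 6-months study period (intervention), followed by standard bathing during the second 6-months period"; the same pair of periods then repeats. The order is fixed and public. No randomisation or concealment is described.

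**Entry.** Section 5.5 lists parental consent as an inclusion criterion and parents' "refusal to sign informed consent" as an exclusion criterion. The synopsis confines the study bath to enrolled infants: "all infants admitted to the NICU and enrolled in the study will be bathed three times a week" with chlorhexidine in the first period.

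**Who is followed.** Under section 5.7, infants admitted during the study and "meeting the inclusion criteria, will be recorded and assigned a specific study number". Daily review of cultures and antibiotic orders "will be performed for all study participants". The same section collects data on intravascular devices, mechanical ventilation and feeding tubes.

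**Comparison.** Outcome A in section 5.6 counts infection events "per 1000 patient days during the intervention periods compared with the control periods". Section 5.9 compares rates between the two kinds of period and names no adjustment for infant risk.

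**Blinding.** Section 5.7 states: "Infectious events will be evaluated by an independent investigator blinded to the intervention period". Nothing is said about blinding parents or recruiting staff.

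**Existing surveillance.** The control rate in section 5.9 is "based on our ongoing surveillance", so the unit already produces a bloodstream infection (BSI) rate.

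**The concern.** The design relies on infants in chlorhexidine periods resembling those in control periods. Admissions may be similar, but the analysed infants are those whose parents agreed. The decision need not look the same in both kinds of period. Sections 6.0 and 6.1.1 cite a label caution about skin injury in premature and very young infants, whereas the control bath is the unit's existing practice. Section 3 says infection risk rises with lower gestational age and birth weight, and with ventilation and central catheters. If parents of such infants agree less often when chlorhexidine is in use, high-risk infants drop out of one side of the comparison only, and chlorhexidine looks protective without being so. The opposite pattern would hide a benefit. This selection happens before any event is assessed, so blinded adjudication does not touch it.

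**Working it through.** **1. The plan's own figure.** Inputs from section 5.9: control rate 2–3 BSI per 1000 patient-days (midpoint 2.5), 50% reduction, 80% power, level 0.05.

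n per group = (z₀.₉₇₅ + z₀.₈₀)² × (λ₁ + λ₂) / (λ₁ − λ₂)² = 7.849 × 0.00375 / 0.00125² ≈ 18,837.

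The two-proportion formula gives 18,801. Both lie within 2% of the stated 18,548, so the figure reproduces with a two-sided test at the midpoint rate. (A one-sided test at 2 per 1000 gives 18,519, also close; nothing below depends on which was used.)

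The requirement of 37,096 days is 37,096 / (2 × 45,000) = 41% of the two-year census. The census covers the whole unit, so the target can be met with well over half of the unit's days outside the study. Sample size therefore does not force near-complete enrolment.

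**2. Bias when chlorhexidine has no effect.** The protocol gives no consent rates or risk strata, so everything here is assumed. Let 30% of eligible patient-days be high-risk, with R times the low-risk BSI rate. Consent in control periods does not depend on risk. Consent in chlorhexidine periods is cL (low-risk) and cH (high-risk).

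Observed ratio = [(0.7·cL + 0.3·cH·R) / (0.7·cL + 0.3·cH)] / (0.7 + 0.3·R)

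| cL | cH | R = 2 | R = 3 |
|---|---|---|---|
| 80% | 40% | (0.80/0.68)/1.3 = 0.905 | (0.92/0.68)/1.6 = 0.846 |
| 90% | 70% | (1.05/0.84)/1.3 = 0.962 | (1.26/0.84)/1.6 = 0.938 |
| 70% | 80% | (0.97/0.73)/1.3 = 1.022 | (1.21/0.73)/1.6 = 1.036 |

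A true ratio of 1 thus appears as about 0.85 to 1.04. If the true ratio were the planned 0.5 in both strata, the same factors would give 0.5 × 0.846 = 0.42 to 0.5 × 1.036 = 0.52.

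**3. Effect on the test.** Control rate 2.5 per 1000, R = 3, cL = 80%, two-sided 5% test, normal approximation, no true effect:

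| cH | Observed ratio | Rejection, 18,548 days per group | Rejection, 45,000 days per group |
|---|---|---|---|
| 60% | 0.929 | 6.4% | 8.4% |
| 40% | 0.846 | 12.1% | 22.6% |

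The larger size is the two-year census split equally and is an upper limit. More patient-days make a false rejection more likely, because the bias stays while the standard error shrinks.

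**The case against.** **Timing and content of consent are not visible.** A reader might infer that parents are approached only once the period's bath is in use, or that control-period parents agree to no more than usual care and data collection. The protocol says neither, and consent pages were removed from the text available. One form covering both baths may already exist and cannot be called missing. What remains is that the calendar is open, so the current bath can be known.

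**The plan collects relevant data.** A reader might infer that the bias would go unseen. That is too strong. Device, ventilation and feeding-tube data in section 5.7 would reveal part of any shift in the risk mix of enrolled infants and allow adjustment. Without counts of infants whose parents declined, though, a shift could not be traced to consent, and unrecorded risk differences would remain.

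**Sensitivity analyses belong in a SAP.** Partly right: a SAP may exist, and the absence of such analyses from the protocol is not itself a fault. The protocol does fix who enters, who is recorded and who is under surveillance, and the risk arises there.

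**The outcome may be meant for the whole unit.** Section 5.6 speaks of patient days without restricting them to enrolled infants, and section 5.9 uses the whole-unit census. The denominator is loosely worded, but section 5.7 ties recording and event review to participants.

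**Size and direction are assumed.** This stands in full. A reader might infer that the bias must favour chlorhexidine; the documents link refusal to infection risk in neither direction. The moderate case (0.94 to 0.96) is small beside the planned ratio of 0.5.

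**Conclusion.** The concern holds as a risk of bias built into the design. It does not show that bias will occur. An open calendar, individual consent, follow-up of participants only and a period comparison together allow the enrolled infants to differ in risk between chlorhexidine and control periods. Neither blinded assessment nor sample size protects against this. The illustrative null ratios of about 0.85 to 1.04 rest on assumed consent rates, a 30% high-risk share of patient-days and a two- to threefold risk. The lower end needs consent to be half as common in high-risk as in low-risk infants, and a threefold risk. Such a distortion would not by itself produce a halving, but it could matter for a smaller observed effect. The safeguards are cheap enough to justify the change; confidence is medium because the consent procedure cannot be seen.

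**What to change.** (a) Beside the analysis of consented infants, pre-specify a sensitivity analysis of the whole-unit BSI rate per 1000 patient-days by period, from the aggregate surveillance cited in section 5.9. Restrict it to infants meeting the age and weight criteria only if surveillance can be broken down that way and the ethics committee agrees, because the restriction needs age, weight, days and events for infants whose parents declined.

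(b) Compare intravascular devices, ventilation and feeding tubes between chlorhexidine and control periods, and adjust the rate comparison for them. Status at study entry is preferable, since later device use can follow from an infection.

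(c) Report anonymous numbers eligible and consenting in each period, and confirm that the same consent wording is used in all four. The counts alone correct nothing, but they help interpret (a) and (b).

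**Cost.** One or two extra analyses, a simple count, and ethics agreement to use aggregate data. The whole-unit rate is a coarse check. It is diluted by ineligible infants: if a share s of control-period BSI events arises in consenting infants and other infants are unaffected, a true ratio of 0.5 appears as 1 − 0.5·s. It may also miss clinical sepsis, which is part of the primary outcome in section 5.2. It should be read for consistency of direction and should not replace the main analysis.
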